## Abstract

**Background:**

Antiviral therapy has been reported to be associated with lower recurrence rate of hepatocellular carcinoma (HCC) for patients with hepatitis B virus (HBV) infection. While entecavir (ETV) and tenofovir disoproxil fumarate (TDF) were both recommended as first-line therapies for HBV patients, recent retrospective studies proposed a lower incidence rate of HCC occurrence or recurrence in those receiving TDF compared ETV. However, the survival benefits of switching to TDF therapy after prolonged ETV treatment before surgery remain uncertain. We delineate the rationale and design of SWITE, a randomized, open-label, phase III trial contrasting TDF switch therapy versus ETV maintenance in HBV-related HCC patients.

**Methods and analysis:**

This is a prospective, randomized, controlled, single-center study with two parallel groups of patients with HBV-related HCC who have received long-term ETV therapy before surgery. West China Hospital will enroll 238 patients, randomized in a 1:1 ratio to TDF switch therapy or ETV maintenance after surgery. The primary endpoint of this study is 3-year recurrence free survival (RFS), with the secondary endpoint being 3-year overall survival (OS) after curative surgery of HCC. Safety events will be diligently recorded.

**Ethics and dissemination:**

The study protocol aligns with the ethical guidelines of the 1975 Declaration of Helsinki. It was approved by ethics committee of West China Hospital (approval number: 2022-074) and was registered with chictr.org.cn (chiCTR2200057867). Informed consent will be obtained from all participants. The results of this trial will be published in peer-reviewed journals and presentations at national and international conferences relevant to this topic.

**Trial registration:**

chiCTR2200057867. Date of registration is March 20 2022.

## Introduction

Hepatocellular carcinoma (HCC) stands as a prevalent malignancy globally [1]. In China, the elevated crude mortality rate of HCC ranks it as the second leading cause of cancer-related death nationally, primarily attributed to endemic chronic hepatitis B virus infection (CHB) [2]. Between 2010 and 2014, the 5-year relative survival rate for Chinese HCC patients was a mere 14.1% [3]. Despite liver resection being the primary treatment for HCC, particularly for those in the early stages with well-preserved liver function, the clinical outcome remains unsatisfactory due to a high recurrence rate. Even in the early stages of HCC, the postoperative 5-year recurrence rate can range from 50 to 70% [4, 5]. Prognostic factors such as tumor size, microvascular invasion, liver cirrhosis, alpha-fetoprotein (AFP) levels, and the viral replication status of HBV influence HCC prognosis [6], with viral load being the most clinically manageable.

Numerous studies have reported that antiviral therapy is associated with a lower HCC recurrence rate after surgical resection [7–9]. For instance, a national cohort study of 4569 patients comparing those with antiviral therapy and untreated patients with resected HBV-related HCC found antiviral therapy to be an independent predictor for lower HCC recurrence [10]. Even in a randomized controlled trial involving patients with low HBV DNA levels, antiviral therapy significantly correlated with improved overall survival (OS) and recurrence-free survival (RFS) [11].

Entecavir (ETV) and tenofovir disoproxil fumarate (TDF) are recommended as first-line therapies for suppressing viral replication [12, 13], demonstrating long-term efficacy in reducing HCC risk for CHB patients [14, 15]. Recent studies on ETV and TDF for preventing recurrence after curative resection in HBV-related HCC consistently favor TDF [16, 17], aligning with our previous findings [18–20]. However, in the majority of these studies, antiviral therapy was initiated only after HCC diagnosis, as the patients had not been diagnosed with HBV infection before. Whether ETV or TDF treatment after curative resection results in different prognostic outcomes in CHB patients who received long-term ETV treatment prior to HCC development remains unclear. Additionally, these studies were prone to bias due to their retrospective nature. Hence, we aim to conduct a prospective randomized controlled study (SWITE) in a single center to directly investigate the effect and safety of switching from ETV to TDF for patients with prolonged ETV therapy before surgery.

## Methods and analysis

### Aims of the study

The study aims to (1) directly compare the efficacy of maintaining ETV and switching to TDF on HCC recurrence risk and survival in patients with prolonged ETV therapy before surgery, (2) compare the safety of ETV maintenance and TDF switch after surgery through adverse event records, and (3) offer evidence and guidance for perioperative antivirus strategies in HBV-related HCC patients with prolonged ETV therapy.

### Study design

This trial adopts a prospective, randomized, controlled, single-center design and is scheduled to commence at West China Hospital from May 2022 to August 2027. Figure 1 illustrates the study process.

**Fig. 1 Fig1:**
[figure not shown]
Flow chart of the study design

### Trial registration

This study was registered with chictr.org.cn (chiCTR2200057867).

### Participant recruitment

From May 2022 to May 2024, patients with HBV-related HCC who have received long-term ETV therapy before surgery that scheduled for hepatectomy in West China Hospital will be screened for eligibility for this trial.

### Inclusion criteria

The inclusion criteria are as follows: (1) aged 18 to 70; (2) newly diagnosed with HBV-related HCC following clinical diagnosis criteria of the American Association for the Study of Liver Diseases (AASLD) [21]; (3) Barcelona Clinic Liver Cancer (BCLC) stage 0 or A, receiving curative liver resection or ablation; (4) ETV monotherapy for over 1 year with pre-surgery HBV-DNA load under 100 IU/mL; (5) Child-Pugh class A with or without cirrhosis, Eastern Cooperative Oncology Group (ECOG) performance status (PS) score ≤ 1; (6) appropriate renal function (serum creatinine < 124 mmol/L).

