### Exclusion criteria

The exclusion are as follows: (1) recurrent HCC; (2) concurrent HCV, HIV, or other serious infections; (3) other malignancies or mental illness; (4) prior anti-tumor therapies pre-surgery, including portal vein ligation/embolization, radiofrequency ablation, transarterial chemoembolization, etc.; (5) participation in conflicting ongoing trials.

Participants can withdraw at any time, and poor compliance may lead to removal. Withdrawal reasons will be recorded in case report forms (CRFs), and data will be analyzed following the intention-to-treat principle [22].

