### Intervention

Participants will be equally randomized into two groups: the experimental group (postoperative antivirus strategies with switch-TDF therapy) and the controlled group (postoperative antivirus strategies with continuing-ETV therapy). TDF dosage is 300 mg per day, and ETV dosage is 0.5 mg per day.

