### Follow-up

Patient follow-up begins post-hospital discharge. Visits to the surgical team will occur every 3 months during the first 3 years post-surgery. Check-ups, including CT and/or MRI, ultrasound, routine blood tests, liver and kidney function assessments, AFP, PIVKA, and HBV DNA level measurements, will be conducted at each visit (Table 1).

**Table 1 Tab1:** Participant timeline

	Study period												
	Enrollment/allocation	Post-allocation											Close-out
Timepoint	Pre-allocation	0 months	1 month	3 months	6 months	9 months	12 months	15 months	18 months	21 months	24 months	30 months	36 months
**Informed consent:**	×												
**Eligibility screen**	×												
**CT or MRI**	×												
**Laboratory test**	×												
**Allocation**	×												
**Surgery**		×											

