As established earlier, antiviral therapy is linked to a reduced HCC recurrence rate post-surgical resection. Current evidence leans towards TDF as a superior choice over ETV in improving HCC prognosis after curative surgery. The potential mechanism behind the lower HCC recurrence rate with TDF therapy, as opposed to ETV therapy, may be attributed to higher serum interferon (IFN)-λ3 levels induced by TDF, but not ETV [32]. IFN-λ has demonstrated antitumor activity in murine HCC models [33, 34], potentially accounting for the divergent recurrence rates observed in patients treated with TDF versus ETV. In a separate in vitro study, TDF pretreatment, unlike ETV, inhibited enteric lipopolysaccharide-mediated production of interleukin (IL)-10 [35], while inducing IL-12. IL-10, an inhibitor of CD8+ T cells, is suppressed, and IL-12 directly stimulates T cells and natural killer (NK) cells. Consequently, TDF therapy may restore the functionality of T cells and NK cells through down-regulating IL-10 and up-regulating IL-12 [16].

Despite prior studies highlighting a superior prognosis with TDF treatment post-surgical resection compared to ETV treatment, these investigations were retrospective and failed to address the necessity of transitioning to TDF therapy after prolonged ETV use. Notably, in China, a nation with a high prevalence of CHB, ETV remains the predominant antiviral drug, constituting nearly 80% of antiviral agents purchased by patients [36]. In clinical practice, many HBV-related HCC patients undergo prolonged ETV therapy before an HCC diagnosis, with TDF potentially overlooked due to economic constraints and concerns about TDF-related renal dysfunction and decreased bone density. Consequently, this study aims to ascertain whether transitioning to TDF treatment post-hepatectomy provides benefits for patients who have received prolonged ETV therapy before surgery. We anticipate that the findings of this study will furnish valuable clinical insights for future treatments.

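### The only renal entry limit is printed as serum creatinine below 124 mmol/L, which no patient can reach, so number and unit cannot both be right

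*Protocol article*

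**What the plan says.** In the protocol article, section Inclusion criteria, item (6) requires "appropriate renal function (serum creatinine < 124 mmol/L"). This is the only entry criterion that concerns the kidney. The other five inclusion items cover age, diagnosis, tumour stage and treatment, prior ETV with viral load, and liver function with performance status. The Exclusion criteria section has five items and ends with "5) participation in conflicting ongoing trials"; none of them mentions creatinine, creatinine clearance or eGFR.

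Three other places bear on the point:

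- Intervention assigns TDF to "the experimental group (postoperative antivirus strategies with switch-TDF therapy"), which is half of the patients under 1:1 allocation.
- Discussion gives "concerns about TDF-related renal dysfunction and decreased bone density" among the reasons why TDF may be overlooked in practice.
- Follow-up schedules "routine blood tests, liver and kidney function assessments" at each visit. Table 1 in that section also lists a laboratory test and an eligibility screen before allocation. No numerical renal limit is attached to any of these.

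**The concern.** An eligibility threshold decides, patient by patient, who may be randomised. A threshold that every possible value satisfies makes no such decision. The criterion then conflicts with its own description, which speaks of appropriate renal function.

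This matters more here than for most laboratory limits, because the article itself links the experimental drug to renal dysfunction, and comparing safety between the arms is its second stated aim. With the limit as printed, a reader cannot tell which range of renal function the trial population covers, or to which patients the safety results will apply. If the same text were used for screening and followed literally, patients whom the criterion was evidently meant to keep out would qualify for randomisation.

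**Working it through.** **Nature of the figure.** The limit is a stated threshold. The article does not derive it from other inputs, so there is no calculation of its own to reproduce. The check is a unit conversion followed by a test of whether the limit can exclude anyone.

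**Inputs**

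- Printed limit: 124 mmol/L (Inclusion criteria, item 6).
- Molar mass of creatinine: 113.12 g/mol. This is a chemical constant and is not given in the article.
- Illustrative range of patient values: 50 to 5,000 µmol/L. This is an assumption, not a figure from the article. It is chosen to run from normal to far beyond severe renal failure.

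**Step 1: convert the limit as printed**

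- 124 mmol/L × 1,000 = 124,000 µmol/L
- 0.124 mol/L × 113.12 g/mol = 14.03 g/L
- 14.03 g/L × 100 = about 1,403 mg/dL

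**Step 2: convert the same number with the smaller prefix**

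- 0.000124 mol/L × 113.12 g/mol × 100 = about 1.40 mg/dL

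The two readings differ by exactly 1,000, the ratio of the two unit prefixes.

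**Step 3: test whether the printed limit can exclude anyone**

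| Assumed creatinine (µmol/L) | In mmol/L | Below 124 mmol/L? | Printed limit ÷ value |
|---|---|---|---|
| 50 | 0.05 | yes | 2,480 |
| 100 | 0.1 | yes | 1,240 |
| 500 | 0.5 | yes | 248 |
| 1,000 | 1.0 | yes | 124 |
| 5,000 | 5.0 | yes | 24.8 |

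Every value in the range passes. Even at the extreme upper end, the limit is still about 25 times the patient's value.

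**Step 4: look for a compensating rule.** Neither list of criteria has another renal item, and the limit is not stated a second time anywhere in the article. The kidney tests in Follow-up take place after allocation. The pre-allocation laboratory test in Table 1 would make a creatinine result available, but the only rule to apply to it is item (6).

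**Step 5: does the point reach the design figures?** The sample size rests on 3-year RFS of 70% against 85%, one-sided alpha 0.05 and 80% power. The two-proportion formula without continuity correction gives 95 per group, so 2 × 95 = 190 as stated. Allowing for dropout, 190 / (1 − 0.20) = 237.5, rounded up to 238 as stated. Creatinine enters neither calculation.

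**The case against.** The strongest reply is that this is an obvious one-letter slip with no demonstrated consequence. The criterion's own words ask for appropriate renal function. The number 124 reads naturally with a different prefix, and screening staff would have a laboratory result in front of them before allocation. The article condenses a full protocol and a CRF that are not shown, and these may carry the correct unit. Typesetting or text conversion could also have changed the character, although ≤ and λ appear correctly elsewhere in the same text.

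Much of this stands. The documents do not show that the rule applied at screening is wrong. What does not stand is that the text can be left alone. An operative entry threshold is misstated, and nothing in the article confirms whether the number or the unit is at fault.

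Three stronger readings are tempting, and the documents support none of them:

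- **That patients with impaired renal function were enrolled.** A reader might infer this from a limit that excludes nobody. The article reports no enrolment data and does not show that anyone applied the limit literally.
- **That the renal safety comparison is confounded.** Randomization and allocation specifies 1:1 block randomisation. A loose limit would admit such patients to both arms alike in expectation. It could widen the population or add noise, but it does not bias the comparison.
- **That the limit is a thousand times any value seen in a patient.** The factor of 1,000 is the ratio between the two units. The distance from patient values varies, from 24.8 to 2,480 times over the assumed range.

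**Conclusion.** The criterion is wrong as written. At about 1,400 mg/dL, the printed limit lies far above any value a patient can have, so the only renal entry criterion excludes nobody when read literally. The unit conversion rests only on the molar mass of creatinine. The finding that nobody is excluded rests on patient values staying below the printed limit, which they do by a wide margin over the assumed range.

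A slip in the unit prefix is the likely explanation, but only the sponsor can confirm it, and it may be confined to the article. The effect on actual enrolment is unknown. The primary endpoint and its analysis are also untouched. What is at stake is a clear definition of who may enter a trial that assigns TDF, and of the renal population to which its safety results apply.

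**What to change.** 1. The sponsor compares criterion (6) with the full protocol and the CRF eligibility check, confirms which number and unit apply, and corrects the article so that the two agree. This is a one-line correction.
2. Only if the full protocol or the CRF carries the same error: correct those documents too, and list the baseline creatinine of all enrolled patients against the confirmed limit. Recruitment was scheduled from May 2022 to May 2024, so patients may already have been randomised. Table 1 schedules laboratory tests before allocation; if creatinine was among them, the listing needs no new data.

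The sample size and the analysis need no change on this account. No renal limit is proposed here; that is for the sponsor to confirm.

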### Exclusion criteria

The exclusion are as follows: (1) recurrent HCC; (2) concurrent HCV, HIV, or other serious infections; (3) other malignancies or mental illness; (4) prior anti-tumor therapies pre-surgery, including portal vein ligation/embolization, radiofrequency ablation, transarterial chemoembolization, etc.; (5) participation in conflicting ongoing trials.

Participants can withdraw at any time, and poor compliance may lead to removal. Withdrawal reasons will be recorded in case report forms (CRFs), and data will be analyzed following the intention-to-treat principle [22].

### Sample size calculation

The sample size calculation was performed using the software PASS (version 2015). The parameters were obtained from our previous randomized clinical trial, which evaluated the efficacy of TDF and ETV in early-stage HBV-related HCC patients after surgery. In that study, the 3-year RFS rates were 70.4% and 82.4% for patients receiving ETV and TDF, respectively. Assuming 3-year RFS rates of 70% for the control group and 85% for the treatment group, with a one-sided alpha of 0.05 and 80% power, the corresponding sample size is 190. Accounting for a 20% dropout rate, a total of 238 patients will be included in this study.

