### Randomization and allocation

Block randomization with a block length of four will be employed. For each block, enrolled participants will undergo 1:1 randomization into the continuing-ETV therapy group and the switch-TDF therapy group. Randomization numbers will be generated using STATA/SE 15.1 and sealed in envelopes.

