### Endpoints

The primary endpoint is 3-year RFS, defined as the interval from the operation to the date of the first diagnosed HCC recurrence, recorded in months. The secondary endpoint is 3-year OS, defined as the interval from surgery to death or the date of the last follow-up, recorded in months.

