### Statistical analysis

Background measures will be presented as mean ± standard deviation for continuous variables or as numbers/percentages for categorical variables. Continuous variables will be compared using a two-sided student *t*-test or Mann-Whitney *U* test, while categorical variables will undergo the chi-square test or Fisher’s exact test. Patient survival (RFS and OS) will be calculated via the Kaplan-Meier method with log-rank test. In particular, cancer-specific survival will also be calculated since decompensation serves as a competing event from HCC recurrence for death. Stage of cirrhosis, tumor burden, antiviral regimen, and other factors which may affect survival after surgery would be considered when conducting survival analysis. Generalized linear models will analyze primary and secondary endpoints. An ITT analysis, including protocol deviations, will be conducted using IBM SPSS version 26.0 software. A *p*-value < 0.05 indicates statistical significance.

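### The one-sided 5% level used to size the trial is not carried into the final p < 0.05 rule, and the 85% TDF rate exceeds the 82.4% of the trial said to supply it; power is below 80% if either is read less favourably.

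*Protocol article*

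**What the plan says.** All references are to the protocol article.

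- **Sample size calculation, origin of the inputs:** "The parameters were obtained from our previous randomized clinical trial". The results of that trial follow: "In that study, the 3-year RFS rates were 70.4% and 82.4% for patients receiving ETV and TDF, respectively".
- **Sample size calculation, rates used:** "Assuming 3-year RFS rates of 70% for the control group and 85% for the treatment group".
- **Sample size calculation, level, power and size:** the same sentence goes on to derive the number of patients "with a one-sided alpha of 0.05 and 80% power, the corresponding sample size is 190". The allowance for loss comes next: "Accounting for a 20% dropout rate, a total of 238 patients will be included in this study".
- **Randomization and allocation:** "enrolled participants will undergo 1:1 randomization into the continuing-ETV therapy group and the switch-TDF therapy group".
- **Endpoints:** "The primary endpoint is 3-year RFS, defined as the interval from the operation to the date of the first diagnosed HCC recurrence".
- **Statistical analysis:** RFS and OS are to be described by Kaplan-Meier curves and compared by a log-rank test. Generalized linear models are also named for the primary and secondary endpoints. The decision rule is that a p-"value < 0.05 indicates statistical significance". No direction is given for the log-rank test, the models or this rule. The term two-sided appears once in the section, attached to the t-test for continuous variables.

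**The concern.** The plan fixes a design level and a decision threshold, and the two are not tied together. The design level is one-sided 0.05. The threshold is p < 0.05 with no direction, applied to methods whose ordinary software output is two-sided: the log-rank statistic is a chi-square on one degree of freedom, and generalized linear models conventionally report two-sided p-values. An analyst who follows the analysis section as written would most likely run a two-sided 5% test on a trial sized for a one-sided 5% test.

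The second matter stands whichever way sidedness is settled. The section says its parameters came from the earlier trial, but the calculation widens that trial's difference from 12.0 to 15 points, a quarter more, without a reason. Both changes (70.4% to 70%, 82.4% to 85%) go in the direction that reduces the sample size.

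A null result would be read as coming from a trial with 80% power when the power may be nearer 50–75%. In the other direction, if sidedness is still open when the data are seen, a result with one-sided p = 0.04 (two-sided 0.08) could be called positive or negative by choice. The Mid-term analysis section plans an efficacy look that may stop the trial, so the question arises before the final analysis.

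**Working it through.** **Inputs.** From Sample size calculation: p1 = 0.70 and p2 = 0.85 (assumed); 0.704 and 0.824 (earlier trial); one-sided alpha 0.05; power 80%; dropout 20%. From Randomization and allocation: 1:1. Normal quantiles: 1.645 (one-sided 0.05), 1.960 (two-sided 0.05), 0.8416 (80% power).

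**Step 1. Reproduce the plan's figure.** For a two-proportion z-test with pooled null variance and no continuity correction, with p̄ = (p1 + p2)/2:

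n per arm = [z_α·√(2p̄(1−p̄)) + z_β·√(p1(1−p1) + p2(1−p2))]² / (p2−p1)²

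Here p̄ = 0.775, 2p̄(1−p̄) = 0.34875 (root 0.5906), and p1(1−p1) + p2(1−p2) = 0.21 + 0.1275 = 0.3375 (root 0.5809).

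- One-sided: [1.645 × 0.5906 + 0.8416 × 0.5809]² / 0.0225 = 94.8, so 95 per arm and **190** in total. This matches.
- Dropout: 190/0.8 = 237.5, so **238**. This matches.
- Two-sided: with 1.960 in place of 1.645, 120.5, so 121 per arm and 242 in total (303 with 20% dropout). This does not match, so the plan's figure was computed one-sided.

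**Step 2. Power at the planned size.**

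Power = Φ{ [(p2−p1)·√n − z_α·√(2p̄(1−p̄))] / √(p1(1−p1) + p2(1−p2)) }

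For 70% versus 85% with n = 95 per arm, (p2−p1)√n = 0.15 × 9.747 = 1.462:

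- one-sided: (1.462 − 0.971)/0.581 = 0.845, power 80.1%
- two-sided: (1.462 − 1.157)/0.581 = 0.524, power 70.0%

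For 70.4% versus 82.4%, p̄ = 0.764, the roots are 0.6005 and 0.5945, and 0.12 × 9.747 = 1.170:

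- one-sided: (1.170 − 0.988)/0.5945 = 0.306, power 62.0%
- two-sided: (1.170 − 1.177)/0.5945 = −0.012, power 49.5%

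**Step 3. Credit all 238 patients.** Dropouts contribute follow-up to a log-rank test, so 190 evaluable is a pessimistic count. Assume exponential times with proportional hazards, 119 per arm, 36 months of follow-up and 20% lost evenly over that time; the plan does not give a loss pattern. The hazard ratios are ln 0.85/ln 0.70 = 0.456 and ln 0.824/ln 0.704 = 0.552. Simulated two-sided log-rank power is about 76–77% for 70% versus 85% and about 55–56% for 70.4% versus 82.4%. As an upper limit, with no dropout at all, the two-proportion formula at 119 per arm gives 79.5% and 58.8% two-sided.

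| 3-year RFS, ETV vs TDF | Sidedness | 190 evaluable | All 238, log-rank, 20% uniform loss | All 238, no loss (two proportions) |
|---|---|---|---|---|
| 70% vs 85% | one-sided | 80.1% | – | 87.4% |
| 70% vs 85% | two-sided | 70.0% | 76–77% | 79.5% |
| 70.4% vs 82.4% | one-sided | 62.0% | – | 70.6% |
| 70.4% vs 82.4% | two-sided | 49.5% | 55–56% | 58.8% |

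At the source rates no cell reaches 80%, even one-sided with nobody lost.

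**The case against.** The other side has a good case on several points.

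- **No two-sided rule is stated.** A reader might infer that the plan prescribes a two-sided log-rank test and so contradicts its design outright. The text does not say so: two-sided belongs to the t-test only. If p < 0.05 is applied one-sided, the stated alpha and power agree for 70% versus 85%. This stands. The defect is an unstated sidedness that does not connect to the one-sided design; the two-sided reading rests on usual practice.
- **The arithmetic is right.** A reader might infer a miscalculated sample size. Step 1 shows otherwise: 190 and 238 follow exactly from the stated inputs.
- **The 85% is introduced as an assumption**, and the source rates are printed beside it. This also stands: nothing is hidden, and an optimistic target effect is not in itself an error. What remains is that the opening sentence credits the parameters to the earlier trial, and no reason is given for departing from it.
- **The log-rank test is not clearly the only decision test**, because generalized linear models are also named. True, but their usual p-values are two-sided as well, so the mismatch does not depend on which one decides.
- **The 70% figure is the low end.** With intention-to-treat analysis and censored follow-up, the loss on the design effect may be nearer 4 points than 10. This is why the power is given as a range.
- **Sidedness is often left to an analysis plan.** Here, however, the protocol itself states both a level and a threshold, and they should match within the document.

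The documents do not show that one-sided 0.05 is wrong. It allows a 5% chance of falsely declaring TDF better, against 2.5% in that direction for a two-sided 5% test. That is a disclosed choice of stringency, provided it is carried through.

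**Conclusion.** The concern holds as an inconsistency, not as a calculation error. The one-sided 0.05 level behind the 190 and 238 is not carried into the p < 0.05 rule. The 85% TDF rate also differs, without explanation, from the 82.4% in the trial said to have supplied the parameters.

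The claim that the trial lacks 80% power whatever the reading goes too far. The shortfall is conditional:

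- If p < 0.05 is two-sided, power for the design effect falls by about 4 to 10 points, depending on how much follow-up dropouts contribute.
- If the true rates are those of the earlier trial, the shortfall with 190 evaluable is about 18 points one-sided and about 30 points two-sided.

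The log-rank figures rest on proportional hazards and uniform loss. The figures for 190 rest on the two-proportion test that reproduces the plan's own size.

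**What to change.** Before any efficacy look, including the mid-term analysis:

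1. In Sample size calculation and Statistical analysis, state one level and sidedness for both the design and the primary RFS test. Two-sided 0.05 is preferable, since it is what the named methods normally report and what readers will assume. If one-sided 0.05 is kept, the p < 0.05 rule for RFS must say so.
2. Keep 238 patients. Under two-sided 0.05, restate power as about 70–76% for 70% versus 85% and about 50–55% for 70.4% versus 82.4%. The lower figure of each range is for 190 evaluable patients; the upper is for the log-rank test on all 238 with 20% uniform loss.
3. Correct the sentence that credits the parameters to the earlier trial, so that it says the rates were informed by that trial, and give the reason for choosing 85%.

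The cost is wording only, with no extra patients. The drawback is that the stated power becomes less favourable.
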